### Interventions

LA group: Patients will be placed in a prone position. The surgeon will disinfect, drape, and after localization, will use 1% lidocaine for local infiltration anesthesia.

ESPB group: Patients will be placed in a lateral decubitus position. This position is standard for performing a bilateral lumbar ESPB as it provides optimal ergonomics for the operator, facilitates ultrasound probe placement, and allows for stable needle access to the transverse processes on both sides. An independent nerve block specialist (with over 3 years of experience in ultrasound-guided nerve blocks) will perform a bilateral ESPB in the operating room. The block will be performed at the vertebral level corresponding to the planned surgical level (*i.e*., the level of the vertebral fracture). A curvilinear probe (2–5 Hz) will be selected, and a parasagittal approach (approximately 3 cm lateral to the posterior midline) will be used for localization. The transverse process of the target vertebral level will be located, and a 24 G needle will be inserted in-plane to the surface of the transverse process. After negative aspiration for blood and cerebrospinal fluid, 3 mL of normal saline will be injected to separate the erector spinae muscle from the transverse process to confirm correct placement. A total of 20 mL of 0.25% ropivacaine will be administered at this level to achieve cranio-caudal spread of local anesthetic within the fascial plane. The same procedure will be performed on the contralateral side.

Concurrently, during the performance of the nerve block, the surgical team will use this time to prepare the sterile instruments and mix the polymethylmethacrylate bone cement. Upon completion of the bilateral blocks, the patient will be promptly assisted into the prone position. The surgical field will then be disinfected and draped in the standard fashion. A standardized minimum block-to-incision interval of 20 min will be maintained between the completion of the block and the surgical skin incision to allow for adequate sensory blockade onset.

### Perioperative management

No premedication will be administered to any patient preoperatively. Furthermore, to eliminate its potential confounding effect on the primary pain outcome, no intraoperative sedative or anxiolytic medications (*e.g*., midazolam, dexmedetomidine) will be administered to patients in either group. This standardization ensures that the reported pain scores directly reflect the analgesic efficacy of the assigned intervention (ESPB or local anesthesia) without the influence of altered sensorium. Upon arrival in the operating room, an intravenous line will be established in the upper limb, and electrocardiographic monitoring (non-invasive blood pressure, electrocardiogram, pulse oximetry) will be connected. Patients will undergo the appropriate interventions according to their assigned group. If the patient’s visual analogue scale (VAS) pain score is >3 during the operation, sufentanil 5 μg will be injected intravenously, up to a maximum of 15 μg. Flurbiprofen ester 100 mg will be injected intravenously before the end of the surgery. When patients experience moderate-to-severe pain (VAS > 3) in the ward, tramadol 50 mg will be injected intravenously.

### Adverse event monitoring

Adverse events (AEs) will be systematically monitored from the initiation of the anesthesia intervention until patient discharge. AEs of specific interest include local anesthetic systemic toxicity (LAST), pneumothorax, block failure, nerve injury, significant hemorrhage at the block site, and infection.

AEs will be defined according to standard clinical criteria. LAST will be defined as the acute onset of neurological (*e.g*., metallic taste, perioral numbness, seizures, loss of consciousness) or cardiovascular (*e.g*., arrhythmia, hypotension) symptoms following local anesthetic injection (Van Wicklin, 2025). Pneumothorax will be suspected in the presence of acute-onset pleuritic chest pain, dyspnea, oxygen desaturation, or diminished breath sounds on auscultation, and confirmed by chest X-ray (Harnedy, Foley & Fitzgerald, 2025). Block failure will be defined as the inability to achieve a detectable sensory deficit in the surgical dermatomes *via* pinprick test 20 min after ropivacaine injection. All AEs will be assessed and documented by the attending anesthesiologist and the surgical team.

Management protocol: LAST: In the event of suspected LAST, the “Stop, Call, Lipid” protocol will be initiated immediately: (1) Stop injection of local anesthetic; (2) Call for help; (3) Administer a 20% lipid emulsion bolus (1.5 mL/kg) intravenously over 2–3 min, followed by a continuous infusion (0.25 mL/kg/min). Advanced Cardiac Life Support protocols will be followed, with adjustments (*e.g*., reduced epinephrine dose) as per LAST treatment guidelines (Van Wicklin, 2025). Pneumothorax: For a suspected pneumothorax, supplemental oxygen will be administered immediately. A chest X-ray will be obtained for confirmation. A consulting cardiothoracic surgeon will be notified. For a large or symptomatic pneumothorax, needle decompression followed by chest tube insertion will be performed (Harnedy, Foley & Fitzgerald, 2025). Other AEs: Significant hemorrhage or neurological deficits will be promptly investigated with ultrasound or other appropriate imaging (*e.g*., MRI) and managed in consultation with relevant specialists (*e.g*., neurologists, vascular surgeons).

All AEs, regardless of their relation to the study intervention, will be recorded in the Case Report Form (CRF). Serious AEs will be reported to the Principal Investigator and the Medical Ethics Committee within 24 h.

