### Blinding

Since the LA group requires the surgeon to perform local infiltration anesthesia, it will be impossible to blind the surgeons. Patients, the anesthesiologists responsible for perioperative management, outcome assessors, and statistical analysts will be blinded to group assignment.

A research coordinator will be designated to maintain and distribute randomization numbers and coordinate communication between researchers. After the patient enters the room, the research coordinator will open the envelope and inform an independent anesthesiologist of the patient’s group assignment. This anesthesiologist will leave after the patient’s intervention is completed and will not participate in subsequent research. Another anesthesiologist will be responsible for the patient’s perioperative management. A researcher blinded to group assignment will be responsible for postoperative follow-up.

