### Data collection

Following the provision of written informed consent by the patients, baseline data will be collected. To standardize the procedural timeline and assess the impact of the interventions on workflow, the following time points will be recorded for all patients: the time of entering the operating room (T1), the time of completion of the nerve block or local anesthesia infiltration (T2), the time of surgical skin incision (T3), and the time of leaving the operating room (T4). The ‘anesthesia preparation time’ will be defined as the interval from entering the operating room (T1) to the completion of anesthesia intervention (T2). The ‘total operating-room occupancy time’ will be defined as the interval from entering (T1) to leaving (T4) the operating room. The ‘block-to-incision’ interval (T2 to T3) will also be calculated. The anesthesiologist responsible for the patient’s perioperative management, who is blinded to group assignment, will assess and record the patient’s VAS pain score at three specific timepoints: (1) during trocar insertion into the pedicle, (2) during polymethylmethacrylate bone cement injection, and (3) at the end of the procedure before transferring the patient out of the operating room. The intraoperative incidence of moderate-to-severe pain will be recorded. Postoperatively, the highest intraoperative pain score, patient satisfaction with intraoperative analgesia, and surgeon satisfaction will be obtained. The incidence of rescue analgesia within the first 24 h post-surgery, as well as the time to first mobilization, will be collected by an independent researcher. The incidence of adverse events will be recorded from the initiation of the intervention until patient discharge.

All data will be initially recorded on paper-based CRF. These data will then be entered into an Excel database, with verification performed by two independent individuals. Although an independent data monitoring committee was not established for this single-center trial, data accuracy and protocol adherence will be safeguarded through internal quality control processes under the supervision of the principal investigator and the institutional ethics committee.

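### The adverse-event window most naturally opens before prone turning and draping in the ESPB arm but after them in the LA arm, a small bias against ESPB in a secondary safety comparison

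*Protocol article*

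**What the plan says.** Two sections of the protocol article set the start of adverse-event recording. Adverse event monitoring states: "Adverse events (AEs) will be systematically monitored from the initiation of the anesthesia intervention until patient discharge". Data collection repeats the rule without the word for anesthesia: "The incidence of adverse events will be recorded from the initiation of the intervention until patient discharge". No other start point is given.

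The Interventions section fixes the order of steps in each arm.

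- **LA arm:** "LA group: Patients will be placed in a prone position". Then: "The surgeon will disinfect, drape, and after localization, will use 1% lidocaine for local infiltration anesthesia".
- **ESPB arm:** "ESPB group: Patients will be placed in a lateral decubitus position". The bilateral block follows. Then: "Upon completion of the bilateral blocks, the patient will be promptly assisted into the prone position". And: "The surgical field will then be disinfected and draped in the standard fashion". At least 20 min must pass between the end of the block and the skin incision.

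The Blinding section places allocation ahead of all of this in both arms: "After the patient enters the room, the research coordinator will open the envelope and inform an independent anesthesiologist of the patient’s group assignment".

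Adverse event monitoring also requires every event to go on the case report form whether or not it is related to the intervention. Secondary outcomes lists adverse-event incidence, and its list of event types is introduced as non-exhaustive. The Discussion says the trial seeks to show benefit with no increase in adverse events.

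**The concern.** The start of the window is tied to a step that falls at a different place in the sequence in each arm. Turning prone, disinfection and draping happen to every patient after the allocation has been opened. If the intervention means the injection itself, these steps are observed for adverse events in the ESPB arm and not in the LA arm.

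Because events are recorded regardless of cause, nothing later removes the imbalance. Hypotension, arrhythmia or desaturation on turning would be entered for an ESPB patient, while the same event in an LA patient would precede the window. The direction is systematic, against ESPB. At stake is the between-group comparison of adverse-event incidence, which with 33 patients per arm will be read largely as counts. Leaving out post-allocation events in one arm only also sits poorly with the commitment in Data analysis to analyse everything by intention to treat.

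**Working it through.** **The plan's own figure.** The only computed figure is the sample size, and this point does not depend on it. With 70% against 35%, two-sided α = 0.05 and power 0.80, pooled variance and no continuity correction:

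n = [1.960·√(2·0.525·0.475) + 0.842·√(0.70·0.30 + 0.35·0.65)]² / 0.35² = (1.384 + 0.557)² / 0.1225 ≈ 30.8, so 31 per group and 62 in total. Then 62/0.95 = 65.3, or 66. This reproduces the protocol and does not change with the adverse-event start point.

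**Sequence check (Interventions).**

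| Step | LA | ESPB |
|---|---|---|
| Envelope opened after room entry | before window | before window |
| Turning or placing prone | before window | inside window |
| Disinfection and draping | before window | inside window |
| Anesthetic injection | opens window | opens window |
| Incision onwards | inside window | inside window |

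In ESPB the injection comes before the prone and draping rows; in LA it comes after them.

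**What the intervention means.** Data collection defines T2 as the end of the nerve block or of the infiltration, and treats that moment as the end of the anesthesia intervention. Secondary outcomes likewise equates the assigned anesthesia procedure with the ESPB or the infiltration. Both point to the injection rather than the positioning. The start of the intervention is not among the recorded times T1 to T4.

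**Size, under stated assumptions.** The documents give no adverse-event rates. Let r be the event risk from all other causes, equal in both arms, and q the event risk during turning, disinfection and draping, also equal in both arms but counted in ESPB only.

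- Expected LA incidence = r
- Expected ESPB incidence = 1 − (1 − r)(1 − q)
- Artificial difference = q(1 − r); excess patients = 33·q(1 − r)

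| q | ESPB incidence, r = 5% | Excess of 33, r = 5% | Excess of 33, r = 10% | Chance of Fisher p < 0.05, r = 5% / r = 10% |
|---|---|---|---|---|
| 1% | 5.95% | 0.3 | 0.3 | 0.3% / 1.3% |
| 3% | 7.85% | 0.9 | 0.9 | 0.9% / 2.0% |
| 5% | 9.75% | 1.6 | 1.5 | 2.3% / 3.3% |
| 10% | 14.5% | 3.1 | 3.0 | 10.5% / 9.5% |

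Example: q = 5%, r = 5% gives 33 × 0.05 × 0.95 = 1.57. The last column is the chance of a nominally significant difference when the true risks are identical. With a start point common to both arms, the artificial difference is 0 for every q.

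**The case against.** Four arguments weigh against the point.

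1. **Most listed events cannot arise in the disputed minutes.** Local anesthetic toxicity is defined as following the injection; block failure, block-site hemorrhage, nerve injury, infection and pneumothorax follow a needle or a drug. This stands, and it is the main reason to expect a small effect. What remains is the all-cause recording rule. There is also a labelling wrinkle: hypotension or arrhythmia on turning could meet the toxicity definition in an ESPB patient, who has been injected, but not in an LA patient, who has not.

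2. **The LA window might open at positioning.** Prone placement is described under the Interventions heading, Data collection omits the word for anesthesia, and no section defines initiation. This reading is possible but less natural, given how Data collection and Secondary outcomes describe the anesthesia procedure. If staff could read it either way, that also calls for a clearer start.

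3. **The steps are not equivalent.** ESPB patients are turned after ropivacaine, LA patients before any drug, and Limitations describes a pragmatic comparison of two strategies. An event on turning may be a real effect of the block strategy. This stands in part: such events belong in the ESPB count, but events unrelated to the drug should then be counted in LA too.

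4. **It is one secondary outcome, and the error makes ESPB look less safe, not safer.** This is correct.

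A reader might infer that the rule seriously distorts the safety comparison, by 5 to 10 percentage points. The documents do not support that. They contain no event rate for these steps, the patients are unsedated, and the missed period is short against follow-up to discharge. An excess of that order needs q of about 5% to 10%, for which nothing in the protocol speaks.

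**Conclusion.** The point holds as a minor one. On the most natural reading, the adverse-event window covers prone turning, disinfection and draping in the ESPB arm and omits them in the LA arm, after allocation has been opened in both. The result is a small directional bias against ESPB in a secondary safety comparison.

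Its size rests wholly on assumed rates: about 0.3 to 3 ESPB patients of 33 for a 1% to 10% risk during these steps and a 5% background rate, probably near the low end. A significant difference from this artefact alone is unlikely: at most 3.3% for q up to 5%, and about 10% only at q = 10%. Part of any ESPB excess on turning may be a true effect of the block. The primary outcome, the sample size and the efficacy analyses are untouched.

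**What to change.** In Adverse event monitoring and in Data collection, start recording at T1, entry to the operating room, in both arms, and compare adverse-event incidence on that common window. Continue to date events that can only follow an injection, such as local anesthetic toxicity, from the injection. The common window does not by itself settle how hypotension on turning is labelled, but it ensures that the LA event is at least recorded.

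The cost is one sentence in each of two sections and the matching instruction on the case report form. T1 is already recorded for every patient, and Perioperative management has monitoring connected on arrival, so no extra patients, visits or equipment are needed. The small downside is that a few pre-injection events unrelated to either anesthetic will be recorded.

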#### Secondary outcomes

Anesthesia preparation time: Defined as the time from patient entry into the operating room to the completion of the assigned anesthesia procedure (ESPB or local infiltration).

Total operating-room occupancy time: Defined as the time from patient entry into to exit from the operating room.

Maximum intraoperative pain score: This will be evaluated using the VAS, ranging from 0 to 10, where higher scores indicated greater pain intensity.

Intraoperative patient satisfaction with analgesia: This will be assessed *via* the VAS, ranging from 0 to 10, with higher scores reflecting greater satisfaction with the pain management provided.

Surgeon satisfaction with analgesia: Surgeon satisfaction will be evaluated using the VAS, ranging from 0 to 10, where higher scores represented greater satisfaction with the analgesia.

Incidence of rescue analgesia within the first 24 h postoperatively: This will be analyzed as a binary outcome (yes/no), representing the proportion of patients requiring any supplemental pain medication within the specified timeframe.

Total perioperative opioid consumption: The total consumption of all rescue opioids administered from the start of the procedure until 24 h postoperatively will be recorded. Intraoperative sufentanil and postoperative tramadol doses will be converted to intravenous morphine milligram equivalents (MME).

Time to first mobilization: This will be defined as the time elapsed until the patient is able to get out of bed for the first time following the procedure.

Incidence of adverse events: Adverse events, including local anesthetic toxicity, hemorrhage, nerve injury or infection, and pneumothorax, will be recorded.

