### Limitations

First, conducting the trial at one tertiary hospital may limit generalizability to different surgical teams, patient demographics and institutional protocols. Furthermore, as all ESPB procedures will be performed by a single, experienced operator to ensure consistency, the results may not be fully generalizable to clinical settings where practitioners have varying levels of expertise in ultrasound-guided regional anesthesia. Second, while patients, outcome assessors and data analysts are blinded, surgeons cannot be masked to group allocation, introducing a possibility of performance bias in intra-operative conduct. Third, only ASA II–III adults undergoing single-level lumbar PVP are eligible. Results may not extrapolate to multilevel PVP, thoracic procedures, general-anesthesia cases or patients with severe systemic disease. Fourth, all ESPB procedures in this trial will be performed by a single, experienced nerve block specialist to ensure consistency and technical quality. While this minimizes internal performance variability, it may limit the generalizability of our results to settings where operators have different levels of expertise with ultrasound-guided regional anesthesia. Future implementation of this technique would benefit from standardized training protocols to ensure reproducible efficacy. Fifth, the use of local infiltration as the control intervention, instead of a sham (saline) ESPB, means that our design cannot fully isolate the specific “block effect” from potential non-specific effects or the profound difference in procedural experience between the groups. This was a deliberate choice informed by ethical considerations and our goal to conduct a pragmatic trial comparing two distinct clinical strategies. Finally, outcomes are monitored up to 24 h post-procedure; the study will not capture delayed complications (*e.g*., rebound pain, cement leakage-related irritation) or long-term outcomes such as the development of persistent pain or chronic opioid use.

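### Outcome assessors are declared blinded without exception, but this is untrue for surgeon satisfaction and only partly true for adverse events

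*Protocol article*

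**What the plan says.** All references are to the protocol article.

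- **Blinding.** On surgeons: "it will be impossible to blind the surgeons". The next sentence lists patients and the perioperative anesthesiologists as blinded, and continues: "outcome assessors, and statistical analysts will be blinded to group assignment". No outcome is excepted.
- **Interventions.** In the control arm: "The surgeon will disinfect, drape, and after localization, will use 1% lidocaine for local infiltration anesthesia". In the ESPB arm a separate specialist gives the block, and "during the performance of the nerve block, the surgical team will use this time to prepare the sterile instruments".
- **Adverse event monitoring.** "All AEs will be assessed and documented by the attending anesthesiologist and the surgical team". Every event goes on the case report form whether or not it is judged related to the intervention.
- **Secondary outcomes.** Nine are listed. One is surgeon satisfaction with analgesia: "Surgeon satisfaction will be evaluated using the VAS, ranging from 0 to 10". Another is the incidence of adverse events.
- **Data collection.** The intraoperative pain scores behind the primary outcome are taken by the perioperative anesthesiologist, who is declared blinded. No blinded rater is named for surgeon satisfaction or for adverse events.
- **Limitations.** Outcome assessors are again called blinded, and in the same sentence "surgeons cannot be masked to group allocation, introducing a possibility of performance bias in intra-operative conduct".

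**The concern.** The people whom the plan says it cannot blind are assessors of two secondary outcomes, while the plan says twice that assessors are blinded. The only consequence it admits is performance bias, which concerns how care is delivered. Detection bias, which concerns how an outcome is rated or classified by someone who knows the arm, is a separate problem and is not mentioned.

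The Discussion makes both outcomes part of the trial's question: whether the block improves surgeon satisfaction, and whether it does so with no rise in adverse events. For satisfaction, the surgeon scores analgesia that the surgeon delivered in one arm and a colleague's block in the other. For adverse events, some criteria leave room for judgement. Examples are hypotension or arrhythmia after local anesthetic as a sign of systemic toxicity, and whether bleeding counts as significant. Staff who know that a block was given may read such signs differently.

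**Working it through.** **1. The plan's own figure.** The only figure that could be touched is the sample size. Inputs from Sample size: 70% versus 35%, two-sided α = 0.05, power 0.80. With the pooled-variance formula and p̄ = 0.525:

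n = [1.960·√(2·0.525·0.475) + 0.842·√(0.70·0.30 + 0.35·0.65)]² / 0.35² = (1.384 + 0.557)² / 0.1225 ≈ 30.8, so 31 per group, 62 in total. Then 62/0.95 = 65.3, so 66. Both match the plan. The figure rests on the primary outcome alone and does not depend on this point.

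**2. Does the surgical team know the arm?** Yes. The surgeon infiltrates in the control arm and does not in the ESPB arm, and the team prepares instruments while the block is being given. The plan itself says that surgeons cannot be blinded.

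**3. Which outcomes does the team assess?**

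| Outcome | Assessor | Blinded as declared? |
|---|---|---|
| Primary: VAS > 3 at any of three timepoints | Perioperative anesthesiologist | Yes, as declared |
| Surgeon satisfaction, 0–10 | Surgeon | No |
| Adverse events | Attending anesthesiologist and surgical team | In part at most |

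That the surgeon gives the satisfaction score is inferred from the outcome's name, because Data collection says only that it is obtained after the operation. A different person collecting the score would not blind the rater.

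**4. Which adverse events could be assessed blind at all?** Block failure is the "inability to achieve a detectable sensory deficit in the surgical dermatomes", tested after ropivacaine, so it can arise only in the ESPB arm. Hemorrhage at the block site presupposes a block. These two reveal the arm whoever records them. Systemic toxicity, nerve injury, infection and pneumothorax do not by definition reveal it.

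**5. How large could the effect on satisfaction be?** The document gives no SD and no basis for a rating preference. As a pure illustration, assume a 1-point preference with no true difference and 33 per arm (df = 64), so t = 1 / (SD·√(2/33)):

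- SD 1.5: t ≈ 2.7
- SD 2.0: t ≈ 2.03, p just under 0.05
- SD 2.5: t ≈ 1.6

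A modest preference could thus cross the 0.05 threshold or miss it, depending on an SD that nobody has stated. The direction is also unknown: the surgeon might favour either arm.

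**The case against.** The strongest reply is that this is a wording gap in a trial openly labelled single-blind, with surgeon unblinding stated twice. Few readers would take a surgeon's own rating as blinded, and that feature is inherent to the outcome. For adverse events, recording regardless of relatedness means that a causality judgement does not decide whether an event counts. Several criteria are also fairly objective: chest X-ray for pneumothorax, a pinprick test for block failure, imaging for suspected bleeding or neurological deficit.

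Much of this stands. It lowers the likely bias in adverse events and rules out some stronger conclusions that a reader might draw:

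- **That adverse events are open-label.** They are assessed jointly with the attending anesthesiologist. If that is the perioperative anesthesiologist of the Blinding section, one of the assessors is declared blinded, so the assessment is mixed.
- **That these results will be presented as blinded.** No passage says so.
- **That surgeon satisfaction should carry no p-value.** The plan never gives it confirmatory status, and dropping the test is a matter of preference.
- **That the illustration measures the bias.** It rests on assumed inputs.

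What the reply does not remove is the conflict in the text. A joint assessment that includes unblinded staff is not a blinded assessment, and the Limitations section repeats the blanket statement at the point where it should have been qualified. Nor is this detail left to a fuller document: the article itself states both who is blinded and who assesses adverse events.

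**Conclusion.** The point holds in a limited form. The plan claims a property, blinded outcome assessment, that its design lacks for surgeon satisfaction and has only in part for adverse events. The acknowledged limitation covers performance bias but not detection bias. Two of nine secondary outcomes are affected. The bias cannot be sized or signed from the document and is probably smaller for adverse events with objective criteria than for the satisfaction score.

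This finding does not affect the primary VAS outcome, sample size, power or α. The conclusion assumes that the surgeon gives the satisfaction score. For adverse events, partly true is the most favourable reading, since it takes the attending anesthesiologist to be the blinded perioperative one. If that is a different, unblinded person, the claim fails for adverse events too.

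**What to change.** 1. In Blinding and in Limitations, restrict the blinded-assessor statement to the outcomes it covers.
2. Label surgeon satisfaction as an unblinded rating. Name detection bias as a limitation when interpreting it and any conclusion that adverse events did not increase.
3. For adverse events that do not themselves reveal the arm, let the surgical team report events and have blinded staff already in place make the recorded classification against the criteria in Adverse event monitoring. In the operating room this would be the perioperative anesthesiologist, and afterwards the follow-up researcher.
4. Label block failure and block-site hemorrhage as unblinded. For item 3 to work, the pinprick test should be done by someone other than the blinded anesthesiologist, because performing it shows the arm.

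The cost is a small added duty for existing staff, since classification goes beyond the follow-up researcher's described role, and a less favourable blinding statement. No change to sample size or primary analysis is needed.
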